### Outcomes

The primary outcome will be beta-cell function at 52-weeks, measured by ISSI-2 [28,29]. The secondary outcomes will be insulin resistance at 52-weeks, measured by HOMA-IR [30], and percentage time in glucose target range at 52-weeks measured by FreeStyle Libre 2 [31]. Additionally, ancillary outcomes of interest will be comparisons between the study arms of the following measures at 52-weeks: (i) further measures of beta-cell function (ΔISR_0–120_/Δgluc_0–120_ × Matsuda index where ISR is the pre-hepatic insulin secretion rate determined by C-peptide deconvolution [32,33], insulinogenic index/HOMA-IR, and fasting pro-insulin/C-peptide ratio [34]), (ii) measures of insulin sensitivity (insulin sensitivity measured by Matsuda index on OGTT [35]), and (iii) anthropometric measures (body weight, body mass index (BMI), and waist circumference). We will also evaluate differences in measures of glucose homeostasis as assessed by isCGM (time above glucose target range (%), time below glucose target range (%), and mean glucose values), by OGTT (fasting glucose, 2-h glucose, area-under-curve of glucose from 0–120 min), and by HbA1c.

### Sample size

The primary outcome requires a sample size of 96 participants. This sample will provide 80% power to detect a 15% difference in ISSI-2 (%) between the study groups at a significant level (alpha) of 0.05. We performed this calculation using an estimated standard deviation of 18% as previously documented in our pilot study [24]. Factoring in an 18% loss-to-follow-up rate, a total of 112 participants, with 56 in each study group, would be required to ensure a minimum of 96 participants.

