### Randomization and intervention

Participants will be randomized 1:1 to either standard lifestyle recommendations or TRE protocol by random number generator (https://www.graphpad.com/quickcalcs/randomize1.cfm). Following randomization, the research coordinator will provide the participants with a booklet containing instruction on healthy eating as per Diabetes Canada Clinical Practice Guidelines [26,27] as well as answer any questions that arise. Participants will undergo metabolic characterization at weeks 0, 12, 24, 36, and 52. Those randomized to the standard group will be told to follow their normal schedule (e.g., possibly consisting of a 16 hour window for eating and ~8 hours of fasting daily). Individuals in the TRE protocol group will be instructed to only eat during a window of 6 hours (2–8 PM) while fasting for the remainder of the day. During the fasting period, participants will only be able to drink water, tea, and coffee (without any sugar added). Between the study visits, participants will be contacted by the research coordinator (virtual visits by phone) for reinforcement of the study protocol and assessment of safety. For 2 weeks after each study visit, participants will also wear an intermittently scanned continuous glucose monitoring system (isCGM) device (FreeStyle Libre 2) on their arms to monitor glucose levels. They will scan the isCGM at least 3 times a day, including before and after each meal. Participants will be instructed to record the time of each meal consumed during these two weeks using the FreeStyle Libre free app. Lastly, individuals who do not have a smartphone or who do not want to use their smartphone will be given a FreeStyle Libre 2 reader.

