### Analysis plan

The primary analysis will be a comparison of the baseline-adjusted ISSI-2 between the study groups and will be evaluated by Students’ *t* test. In addition, given the repeated measures of metabolic characterization over follow-up, we will also evaluate the longitudinal change in ISSI-2 over time between the two study groups by Generalized Estimating Equation (GEE) model. The GEE model will examine (i) ISSI-2 change effect of TRE versus standard lifestyle, (ii) time effect on ISSI-2 changes, and (iii) treatment-by-time interaction (to determine whether ISSI-2 changes differentially over time between the study arms). Statistical analyses will only be performed after all study visits have been completed. No interim analysis is planned. Finally, given the sex differences in body fat deposition, we are planning stratified analyses by biological sex for the primary analysis.

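### The sample-size figures contradict each other: a 15% difference with SD 18% needs 48 participants for 80% power, and 96 would give about 98%

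*Protocol article*

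**What the plan says.** The Sample size section of the protocol article gives a complete calculation:

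- Evaluable number: "The primary outcome requires a sample size of 96 participants".
- Power, target difference and significance level: "This sample will provide 80% power to detect a 15% difference in ISSI-2 (%) between the study groups at a significant level (alpha) of 0.05". Whether alpha is one-sided or two-sided is not stated.
- Variability: "We performed this calculation using an estimated standard deviation of 18% as previously documented in our pilot study".
- Attrition: with 18% lost to follow-up, 112 randomised (56 per group) is said to secure at least 96.

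Two further inputs stand elsewhere in the article. Randomization and intervention fixes the allocation: "Participants will be randomized 1:1 to either standard lifestyle recommendations or TRE protocol". Analysis plan describes the primary comparison: "The primary analysis will be a comparison of the baseline-adjusted ISSI-2 between the study groups", to be tested by Student's t test.

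**The concern.** A two-group comparison of means is fully determined by the difference, the SD, the significance level, the power and the allocation ratio. All five are printed, so the evaluable number can be checked directly, and it comes out at half of what is stated. Rounding or choice of software moves such a number by one or two per arm, not by a factor of two.

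This paragraph is the design justification for the primary outcome. If the SD of 18% is right, readers and the ethics board are told that 96 are required where 48 would meet the stated criterion, and the detectable difference is given as 15 when it is nearer 10. If a larger SD was really used, the power is about as stated, but the printed SD is wrong and the trial has little reserve. The two cases give different pictures of the trial's sensitivity, and the article does not let a reader tell them apart.

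**Working it through.** **Inputs.** Difference 15, SD 18, alpha 0.05, power 80%, N = 96, loss 18%, 112 randomised (all from Sample size); 1:1 allocation (Randomization and intervention); two-sample t test (Analysis plan). Two-sided testing is an assumption; one-sided is tried below.

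**1. Number needed on the stated inputs.** By the normal approximation,

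n per arm = 2 × (1.960 + 0.842)² × (18/15)² = 2 × 7.851 × 1.44 = 22.6, so 23 per arm (46 in total).

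By the t test (noncentral t), n = 23.6, so 24 per arm (48 in total). The power is 78.9% at 23 per arm and 80.7% at 24 per arm. The stated 96 is not reproduced.

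**2. Power at the stated number.** With 48 per arm the noncentrality is (15/18) × √(48/2) = 4.08. The normal approximation gives Φ(4.08 − 1.96) = 98.3%; the t test gives 98.1%. The stated figure is 80%.

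**3. What 96 corresponds to at 80% power.** At 48 per arm the detectable standardised difference is 0.578 (t test). Hence:

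- with SD 18: 0.578 × 18 = 10.4 points;
- with a difference of 15: SD = 15/0.578 = 26.0.

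**4. Could another reading of the inputs give 96?**

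| Variant | Total N |
|---|---|
| One-sided alpha 0.05 | 38 |
| Rank test, efficiency 0.955 to 0.864 | 50 to 56 |
| Log scale, 15% increase | 54 to 56 |
| 90% power | 64 |
| 95% power | 78 |
| Two-sided alpha 0.005 | 82 |
| SD 18 × √2 = 25.5 | 94 |

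Only the last comes near, and it changes a stated input. Adjusting for baseline cannot raise the number, because adjustment does not increase the residual SD. Attrition cannot explain it either, since the article applies attrition after 96.

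**5. Attrition.** 112 × (1 − 0.18) = 91.8, so about 92 evaluable. Keeping 96 at 18% loss needs 96/0.82 = 117.1, that is 118 for equal arms. With 112 randomised, 96 remain only if loss is 1 − 96/112 = 14.3%. With 92 evaluable (46 per arm) and SD 18, power for 15 points is 97.7% and the difference detectable at 80% power is 10.6 points.

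**The case against.** The strongest reply is that the number, the power and the difference may all be right and only the printed SD wrong. With an SD of 26%, 96 participants give 79.9% power for 15 points; with 18 × √2 = 25.5% they give 81.5%. The article does not say whether the pilot's 18% is a between-person SD, an SD of percentage change or a within-person cross-over difference, so a different SD could have been entered from the one printed. This stands. A reader might infer that the power statement is the wrong item, or that the trial is twice as large as it needs to be. The article supports neither; it shows only that the four figures disagree.

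A reader might also guess at a cause, such as a total taken for a per-arm number, or a doubling for the two sexes. Sex-stratified analysis is planned, and 24 per arm in each sex does make 96. But Sample size ties the 96 to the primary outcome and does not mention sex, and the planned recruitment of 67 women and 45 men would not yield 48 of each. Neither cause has support in the text.

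Nor should one say that the 15% difference comes from the pilot. Sample size attributes only the SD to it, and the Introduction reports that ISSI-2 improved there without giving the size.

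Finally, on the printed inputs the discrepancy runs in the safe direction: the trial has more power than claimed, and the test, allocation and data collection are unaffected. That is correct and limits the consequence. It does not make the paragraph consistent, and nothing elsewhere in the article reconciles it.

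**Conclusion.** The point holds as an internal inconsistency in a figure that the trial relies on. On the stated difference, SD, alpha and allocation, 80% power needs 48 participants against 96 stated, and 96 gives about 98% power against 80% stated. Alternatively, 96 and 80% go with 10.4 points at SD 18%, or with an SD of about 26% at 15 points. Two-sidedness is assumed, but one-sided testing only widens the gap.

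Which of number, SD, difference or power is misreported cannot be settled from the article, so whether the trial has ample power or only about the stated 80% is open until the sponsor answers. Separately, the step from 96 to 112 does not hold at the article's own loss rate: it leaves about four participants fewer than stated.

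**What to change.** Keep enrolment as planned. The sponsor should go back to its calculation, establish which inputs were used, and restate the Sample size paragraph accordingly:

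- If SD 18% is right, state about 98% power for a 15-point difference at 96 evaluable, with 80% power for about 10.4 points.
- If a larger SD of about 26% was used, print that SD and its source.
- If 96 was deliberately enlarged for another reason, state that reason.

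State the sidedness of alpha. In the same edit, make the attrition figures agree: either report about 92 evaluable from 112 at 18% loss, with the power figures for that number, or give the loss rate of about 14% at which 112 keeps 96, if that is what is expected.

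The cost is a check of one calculation and a wording change in the protocol. Recruitment, treatment and data collection are not affected.

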### Setting and recruitment

This trial will take place at a single academic center, Mount Sinai Hospital (MSH) in Toronto, Canada. It has received institutional research ethics and board approval (#REB 002) and all participants will provide informed consent form. We will conduct recruitment by contacting eligible participants at MSH, recruiting through nearby family physicians’ offices, and advertising with social media. To enable stratified analyses by sex, a maximum ratio of 1.5 female:male (n = 67 females and n = 45 males) will be recruited. Initial contact with interested participants will be made by one of the patient’s healthcare providers. Following the first interaction, the individuals will then be contacted by our research coordinator to determine eligibility. Potential participants will be emailed a consent form and provided with as much time as needed to review and decide on whether or not they wish to participate.

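### At the stated 18% loss, enrolling 112 is expected to leave about 92 completers rather than a minimum of 96; the effect on power is under two percentage points

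*Protocol article*

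**What the plan says.** All the figures are in the Sample size section of the protocol article.

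- Evaluable number: "The primary outcome requires a sample size of 96 participants".
- Design target: "80% power to detect a 15% difference in ISSI-2 (%) between the study groups at a significant level (alpha) of 0.05", with an SD of 18% taken from the pilot study.
- Attrition and enrolment: "Factoring in an 18% loss-to-follow-up rate, a total of 112 participants, with 56 in each study group, would be required to ensure a minimum of" that same evaluable number.

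Randomization and intervention sets equal allocation ("Participants will be randomized 1:1 to either standard lifestyle recommendations or TRE protocol"), so 96 is 48 per arm. Setting and recruitment divides the same enrolment total by sex ("n = 67 females and n = 45 males"; 67 + 45 = 112). The article gives no other loss rate and no other evaluable target.

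**The concern.** An attrition allowance should make the enrolled number, reduced by the assumed loss, equal the number the analysis needs. Here it does not: reducing 112 by 18% gives fewer than 96. A reader cannot tell whether the trial is planned around 96 completers or 92, or around 18% loss or 14%. The wording also promises a floor, whereas any such calculation gives only an expected number. At stake are the accuracy of the sample-size justification and the power quoted for the number expected to finish a 52-week lifestyle trial.

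**Working it through.** **Inputs.** From Sample size: 96 evaluable, 18% loss, 112 enrolled (56 per arm), difference 15, SD 18, alpha 0.05, power 80%. From Randomization and intervention: 1:1 allocation. From Analysis plan: two-group Student's t test. The article does not say whether alpha is one- or two-sided; two-sided is assumed.

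**Step 1: where 112 may come from.** Multiplying the per-arm number by (1 + loss) gives 48 × 1.18 = 56.64. Truncated, that is 56 per arm, or 112. This reproduces the figure, but the article does not show its method, so the origin is a guess. The method is also not valid: the loss applies to those enrolled, so the required number must be divided by (1 − loss).

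**Step 2: the correct inflation.** 96/(1 − 0.18) = 117.07. Per arm, 48/0.82 = 58.54, rounded up to 59, so 118 in total. The stated 112 is 6 fewer.

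**Step 3: what 112 delivers.** 112 × 0.82 = 91.84, or 56 × 0.82 = 45.92 per arm: about 92 in total and 46 per arm, some 4 below 96.

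**Step 4: the loss that 112 covers.** 1 − 96/112 = 14.3%.

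**Step 5: how firm the minimum is.** If each participant is lost independently with probability 18%, the number of completers is binomial with probability 0.82. The chance of at least 96 is about 19% with 112 enrolled and about 63% with 118. Even the correctly inflated number gives an expectation and not a guarantee.

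**Step 6: effect on power.** Two-sided t test with n per arm, noncentrality = difference / (SD × √(2/n)), degrees of freedom 2n − 2.

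| Difference, SD | 48 per arm | 46 per arm |
|---|---|---|
| 15, 18 (as stated) | noncentrality 4.08, power 98.1% | noncentrality 4.00, power 97.7% |
| 15, 26 (illustrative) | noncentrality 2.83, power 79.9% | noncentrality 2.77, power 78.1% |

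The SD of 26 is not in the article. It is an assumption, chosen because it is about the value at which 96 participants give 80% power for a difference of 15. With SD 18, the difference detectable at 80% power moves from 10.4 points (48 per arm) to 10.6 (46 per arm).

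**Step 7: why the two rows differ so much.** On the stated difference and SD, the exact t calculation reaches 80% at 24 per arm (80.7%; 23 per arm gives 78.9%), or 48 in total. The 96 is therefore twice what its own inputs need. That is a separate question in the same section, but it decides which row of the table applies.

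**The case against.** The best defence is that nothing of substance follows. On the stated inputs the shortfall costs 0.4 percentage points of power (98.1% to 97.7%). In the unfavourable case it costs 1.8 points (79.9% to 78.1%). This stands, and it fixes the severity: the error needs a corrected statement and does not threaten the design.

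Three further limits also stand. First, a reader might infer that the trial is certain to miss 96. The article does not support that: 91.8 is an expected number, and under independent loss 96 or more would still finish in about one trial in five. Second, a reader might count the sex split in Setting and recruitment ("a maximum ratio of 1.5 female:male (n = 67 females and n = 45 males) will be recruited") as another instance. It only divides the enrolment total and makes no statement about attrition or completers, so it is not a separate error. Third, relabelling the allowance as 14% would make the sentence add up, but the article offers no basis for that rate; its only stated expectation is 18%.

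What the defence cannot do is reconcile the sentence. Rounding does not explain a gap of 6, and multiplying by 1.18 may explain how 112 arose without making it yield 96.

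**Conclusion.** The figures 96, 18% and 112 are mutually inconsistent. At the stated loss, 112 enrolled are expected to leave about 92 completers (46 per arm); expecting 96 would take 118 (59 per arm); 112 covers 14.3% loss. This part is plain arithmetic on the article's own numbers.

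The power figures rest on a two-sided test, equal arms and equal loss in both. Under those assumptions the cost is under 2 points whichever inputs prove correct. It would be tempting to conclude that the trial is underpowered and must recruit more. The article does not support that: on its stated difference and SD, 92 participants give 97.7% power. The opposite claim, that 112 is ample in every case, is not supported either, because it holds only if 15 and 18 are the right inputs. If 96 is what 80% power truly needs, 112 gives about 78%. This is a minor arithmetic correction, best made when the 96 is reconciled with its own inputs.

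**What to change.** First settle the difference and SD that the 96 is meant to rest on. Then keep 112 and the 18% assumption, and replace the promise of at least 96 with wording such as: *Allowing for 18% loss to follow-up, enrolment of 112 (56 per arm) is expected to leave about 92 evaluable participants (46 per arm)*. Follow it with the power for 92 from the settled inputs, which is 97.7% if 15 and 18 stand.

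If the settled inputs show that 96 really is needed for 80% power, the sponsor should either report the roughly 78% that 92 gives or enrol 118, the number consistent with expecting 96 at 18% loss. In the second case the split by sex in Setting and recruitment would have to be updated to the new total. A 14% allowance should be stated only with a justification for that rate.

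The cost is one or two sentences in Sample size, with no change to recruitment if 112 is kept. The article says recruitment has only just begun, so the correction can be made before any data are analysed.

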### Setting and recruitment

This trial will take place at a single academic center, Mount Sinai Hospital (MSH) in Toronto, Canada. It has received institutional research ethics and board approval (#REB 002) and all participants will provide informed consent form. We will conduct recruitment by contacting eligible participants at MSH, recruiting through nearby family physicians’ offices, and advertising with social media. To enable stratified analyses by sex, a maximum ratio of 1.5 female:male (n = 67 females and n = 45 males) will be recruited. Initial contact with interested participants will be made by one of the patient’s healthcare providers. Following the first interaction, the individuals will then be contacted by our research coordinator to determine eligibility. Potential participants will be emailed a consent form and provided with as much time as needed to review and decide on whether or not they wish to participate.

### Analysis plan

The primary analysis will be a comparison of the baseline-adjusted ISSI-2 between the study groups and will be evaluated by Students’ *t* test. In addition, given the repeated measures of metabolic characterization over follow-up, we will also evaluate the longitudinal change in ISSI-2 over time between the two study groups by Generalized Estimating Equation (GEE) model. The GEE model will examine (i) ISSI-2 change effect of TRE versus standard lifestyle, (ii) time effect on ISSI-2 changes, and (iii) treatment-by-time interaction (to determine whether ISSI-2 changes differentially over time between the study arms). Statistical analyses will only be performed after all study visits have been completed. No interim analysis is planned. Finally, given the sex differences in body fat deposition, we are planning stratified analyses by biological sex for the primary analysis.

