A recent lifestyle intervention of interest is time-restricted eating (TRE), which involves limiting food intake to a prescribed window of 4−8 hours [16–20]. Unlike traditional diets, TRE does not require calorie counting or specific food regulations/restrictions yet can achieve weight loss comparable to standard calorie-restrictive approaches [21,22]. Beyond weight reduction, TRE can offer additional metabolic benefits by promoting a shift from glucose utilization via glycogenolysis to lipolysis during prolonged fasting which is a pathway less dependent on insulin [23]. This shift suggests TRE may be a particularly relevant tool in managing conditions characterized by hyperinsulinemia (such as insulin resistance). Given its implications for insulin resistance, the impact of TRE on beta-cell function is of interest. To address this question, we recently conducted a randomized cross-over trial in which 39 overweight/obese participants with early T2DM completed 6 weeks of TRE (20 hours fasting/ 4 hours eating) or standard lifestyle [24]. Compared to standard lifestyle, TRE improved beta-cell function (Insulin Secretion-Sensitivity Index-2 (ISSI-2)), reduced hepatic insulin resistance (Homeostasis Model Assessment of Insulin Resistance (HOMA-IR)), and lowered HbA1c (−0.32 ± 0.48%, p < 0.001) [24]. These improvements were accompanied by reductions of body weight (−3.86 ± 3.1%, p < 0.001), and waist circumference (−3.8 ± 7.5 cm, p = 0.003) [24]. The results of this pilot study suggest that TRE is a pragmatic lifestyle intervention that can improve beta-cell function, insulin resistance, and glucose metabolism in overweight patients with T2DM, accompanied by beneficial effects on adiposity and negligible adverse effects. However, the outstanding question that remains is whether this lifestyle intervention can be sustained over time [25]. We are thus performing an open-label, parallel-arm, randomized controlled trial to determine whether TRE over 52-weeks is associated with improvement in beta-cell function, insulin resistance, and glucose homeostasis as compared to standard lifestyle in overweight/obese individuals with early T2DM.

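### The primary analysis names a t test for baseline-adjusted ISSI-2 without defining the adjustment or the scale; ANCOVA on one stated scale would define both and is usually more precise

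*Protocol article*

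**What the plan says.** Three sections of the protocol article bear on the primary endpoint.

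- **Outcomes:** "The primary outcome will be beta-cell function at 52-weeks, measured by ISSI-2". This gives the variable and the time point, but no scale (raw, change, percent change or log).
- **Sample size:** "This sample will provide 80% power to detect a 15% difference in ISSI-2 (%) between the study groups", "at a significant level (alpha) of 0.05", "using an estimated standard deviation of 18% as previously documented in our pilot study". This section alone works in percent. It does not say whether the 18% is the SD of a single value, of a change, of a percent change or of a log value.
- **Analysis plan:** "The primary analysis will be a comparison of the baseline-adjusted ISSI-2 between the study groups and will be evaluated by Students", the test being Student's t test. The adjustment is not defined and no scale is given. The same section adds a second analysis: "we will also evaluate the longitudinal change in ISSI-2 over time between the two study groups by Generalized Estimating Equation (GEE) model". That model is additional, so it does not settle what the primary test is.

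Neither ANCOVA nor a log transformation is mentioned anywhere in the article.

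**The concern.** A two-sample t test compares two means and takes no covariate. To be baseline-adjusted, it must be run on a variable that already contains the baseline value: a change, a percent change, or a residual from a regression on baseline. The article does not say which. These choices estimate different quantities or differ in precision, so the sentence does not define one primary analysis.

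Two things are at stake. The first is precision: baseline ISSI-2 is measured in everyone, and the usual ways of feeding it into a t test use it less efficiently than a regression on it. The second is coherence: the target difference and SD are percentages, and nothing in Outcomes or Analysis plan says that the analysed variable is on a matching scale. A reader therefore cannot check that the power calculation belongs to the test that will be run.

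**Working it through.** **1. The plan's own figure.** Inputs from Sample size: difference 15, SD 18, alpha 0.05 (taken as two-sided), power 80%.

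- n per arm = 2 × (1.960 + 0.842)² × (18/15)² = 2 × 7.85 × 1.44 = 22.6, so 23 per arm by the normal approximation or 24 with the t distribution. That is 46 to 48 in total, against 96 stated.
- At 48 per arm: 15 / (18 × √(2/48)) = 4.08, and 4.08 − 1.96 = 2.12, so power is about 98%.
- Loss: 96/0.82 = 117.1, so 118 would be needed. 112 × 0.82 = 91.8, which is below 96.

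The stated inputs do not yield 96, and 96 with 18% loss does not yield 112. An SD of 18 × √2 = 25.5 would give 46 to 47 per arm, close to 48, but the article does not state it. This matters here because it leaves open what the 18% measures.

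**2. Variance of the candidate analyses.** Let σ be the SD of ISSI-2, equal at baseline and week 52, and r their correlation. The article gives no r; 0.5 to 0.8 is assumed.

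- Change score: 2σ²(1 − r)
- ANCOVA: σ²(1 − r²)
- Ratio of ANCOVA to change: (1 − r²) / [2(1 − r)] = (1 + r)/2

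| r | (1+r)/2 | Reduction in variance |
|---|---|---|
| 0.5 | 0.75 | 25% |
| 0.6 | 0.80 | 20% |
| 0.7 | 0.85 | 15% |
| 0.8 | 0.90 | 10% |

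**3. What this means for power.** Assume log-normal ISSI-2, a true ratio of 1.15 (ln 1.15 = 0.1398), 48 per arm (√(2/48) = 0.2041) and r = 0.5. The log SD is s = √ln(1 + CV²). At r = 0.5 the SD of a log change is s√(2 × 0.5) = s, and the ANCOVA residual SD is s√0.75. The normal approximation is Φ(0.1398 / (SD × 0.2041) − 1.96):

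| Assumed CV | s | Log-change t test | Log ANCOVA |
|---|---|---|---|
| 30% | 0.294 | Φ(0.37) = 64% | Φ(0.73) = 77% |
| 25% | 0.246 | Φ(0.82) = 79% | Φ(1.25) = 89% |
| 18% | 0.179 | Φ(1.87) = 97% | Φ(2.47) = 99% |

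Simulation of the t test on percent change against log ANCOVA gives about 63% against 75% at CV 30%, 79% against 89% at 25%, and 97% against 99% at 18%. A repeat with 20,000 runs agreed to within about two points. At CV 30% and r = 0.7 the gap narrows to about 84% against 90%.

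**4. Validity.** In a separate simulation (normal data, 48 per arm, 8,000 runs), type I error was about 5% for ANCOVA and for t tests on residuals, change and the final value. With an effect of 0.4 SD and r = 0.5, power was 60.4% for ANCOVA, 60.4% for the t test on residuals, 48% for change and 49% for the final value.

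**5. What the remedy does to the sample size.** On the log scale with an analysis SD of about 0.18, 26 to 27 per arm suffice and 48 per arm gives about 97% power. With 0.18 × √2 = 0.255, 53 per arm are needed and 48 give 77%. Neither recovers 48 per arm.

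**The case against.** The strongest reply is that a t test can use baseline. On change, percent change or residuals it is valid under 1:1 randomisation, and on residuals it loses essentially nothing against ANCOVA. That stands. A reader might infer from the wording that the named test cannot make an adjusted comparison, or is invalid. The article does not support this: the fault is that the adjustment is undefined and that its usual forms are less efficient. Nor is an unadjusted week-52 comparison a fair reading, since the text says that baseline is accounted for.

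Second, the power loss comes from assumed inputs. If the 18% in Sample size is read as the CV, every version has about 96% power or more at 48 per arm. That also stands, and so the loss is given as a range. It is not a full answer, because 96 does not follow from an SD of 18% and the article does not say what that SD measures.

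Third, a reader might infer that the three sections contradict one another on scale. They do not: Outcomes and Analysis plan state none, and a 15% difference fits either percent change or a relative difference at week 52. The scale is unspecified, not shown to differ.

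Fourth, this is a condensed article, and an unseen analysis plan may fix the adjustment. A reader might infer that the choice will be made after the data are seen; the article does not show that. But it does name both a test and an adjustment, and that stated pair can be improved whatever detail sits elsewhere.

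**Conclusion.** The point holds in a limited form. The article pairs a test that takes no covariate with an undefined baseline adjustment, and the natural readings of that pair are valid but less precise than ANCOVA. The variance reduction is 10% to 25% for an assumed r of 0.8 to 0.5, relative to a change score. In power at r = 0.5, 48 per arm and a true ratio of 1.15, the gain is about 10 to 12 points if the CV is 25% to 30%, and about 2 points if it is 18%. These figures rest on log-normal data and on an r and CV that the documents do not give.

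It would go too far to say that log-scale ANCOVA is the only remedy or that it repairs the sample size. ANCOVA on untransformed ISSI-2 with a matching sample size would also resolve the ambiguity, and no choice of test makes 96 or 112 follow from the stated inputs. This should be fixed, but it does not threaten the validity of the trial.

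**What to change.** In Analysis plan, replace the t test with ANCOVA: week-52 ISSI-2 regressed on arm and baseline ISSI-2, with the arm effect and its 95% confidence interval as the primary result. State one scale, and use it in Outcomes, Sample size and Analysis plan alike.

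The log scale is a suitable choice because the arm effect becomes a ratio of geometric means, which reads directly as the percent difference in Sample size (15% becomes ln 1.15). If it is chosen, restate the pilot SD on that scale, say whether it is the SD of a single value, a change or a residual, and give the assumed baseline correlation if it is used. The derivation of 96 and 112 needs its own correction.

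The cost is a few sentences and one recalculation from pilot data. Recruitment has only just started and no analysis is planned until all visits are complete, so the change can be made now without compromising the trial. The change of test itself requires no extra participants; whether the restated SD alters the target number depends on its value.
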